## 4.2 Intolerable Toxicity

Intolerable toxicity is defined as:

- An AE that may affect the subject's ability to continue study-specific procedures or is not in the subject's best interest, at the discretion of the investigator or the Sponsor.
- Toxicity requiring more than twice dose reductions of HQP1351.
- HQP1351 allergy and serious allergic reactions (e.g., hypotension, bronchospasm, and/or rash generalised/erythema).

Subjects who experience intolerable toxicity will permanently discontinue the study unless it is in the subject's best interest to continue the study after the investigator has evaluated the subject's risks and benefits and discussed with the Sponsor.

[figure not shown]

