### **4.3 Dose Delay and/or Dose Reduction**

#### **4.3.1 Dose interruption**

Treatment may be interrupted for up to 2 weeks (14 days) to allow study drug-related toxicity to recover to baseline or Grade  $\leq 1$ . For non-treatment-related or unexpected toxicity, whether to discontinue treatment should be decided after discussion between the investigator and the sponsor. If HQP1351 is discontinued for more than 2 weeks (14 days), the subject will be withdrawn from the study. The subject can stay in the study to receive low-dose HQP1351 treatment (determined upon discussion by the principal investigator and the sponsor) if it is considered that the subject can benefit from continuous study treatment.

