#### **4.3.2 Dose adjustment**

AEs that occur during this study will be graded according to National Cancer Institute-Common Terminology Criteria for Adverse Events (NCI-CTCAE) (v4.03). According to the correlation of AEs with the study drug and grade, the investigator will take different actions with the study drug, including maintaining the original treatment regimen, withholding dosing, reducing the dose, and terminating the treatment. Up to twice dose reductions are allowed, each to the next lower dose already explored. Any adult subject requiring a reduction of HQP1351 dose below 30 mg QOD should permanently discontinue the study treatment. The study drug can be resumed when the study drug-related toxicities resolve to grade 1 or below.

Dose adjustment may not be performed for grade 1/2 toxicities related to the study drug that can be treated by supportive treatment or don't influence normal daily activities of subjects, unless QTc prolongation, clinically significant pancreatitis, or other clinical conditions that affect subject's safety at the investigator's discretion. For intolerable (symptomatic or influencing subject's normal daily activities) or persistent (unable to be handled with the best supportive care and recovered to grade 1 or baseline after up to 2-week of drug withdrawal) grade 1/2 toxicities related to the investigational product, whether to make dose adjustment will be determined by discussion between the PI and the sponsor.

If a subject experiences grade 3 or 4 investigational drug-related toxicities, the investigational drug should be interrupted immediately. A maximum of 2 weeks (14 days) of drug interruption is permitted to resolve toxicities to Grade 1 or below, or baseline level. The investigational drug can be resumed when the toxicities resolve to Grade 1 or below, or baseline level. Each subject may undergo a maximum of twice dose reductions throughout the study period, and dose increases are generally no longer allowed after dose reductions. Please refer to Table 2-4 for guidance on dose adjustment for study drug-related toxicity.

[figure not shown]**Table 2: Dose delay and adjustment due to hematologic toxicities**

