### **5.4 Randomization and Blinding**

The randomized part of this study will adopt a randomized and open-label design. The non-randomized part of this study will adopt a non-randomized and open-label study design.

In the randomized part, this study will use the Interactive Web Response System (IWRS) for central randomization. Each subject will be randomly assigned to a 30 mg, 40 mg, or 50 mg dose group. The randomization list used for central randomization will be generated by SAS 9.4 using block randomization and uploaded to the IWRS database. To ensure a balanced number of subjects across dose groups in each phase, the same randomization list will be used at all sites.

Since the randomized part of this study only involves randomization, it is a non-blind open-

[figure not shown]

label trial, and it is not necessary to blind the investigational products according to the generated randomization list.

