## 10 Statistical Analysis

### 10.1 Sample Size Calculation

In the HQP1351 SJ-0002 CML patient study, the MTD has been determined to be 50 mg. But starting from the 12 mg dose group, the drug has shown its efficacy. The study is being expanded at 30 mg, 40 mg and 50 mg to determine the dose groups with the best efficacy/safety ratio. According to the data of HQP1351 SJ-0002 CML patient study, this study has been modified accordingly to randomize subjects into the 30 mg, 40 mg and 50 mg dose groups at the same time, about 10 subjects each.

As of February 2021, HQP1351 has undergone a total of 9 clinical studies, and preliminary results from the Phase I and Phase II clinical trials that have been conducted show a favorable safety profile in the dose range of 50 mg QOD. HQP1351 (olverembatinib tablets) has been granted conditional marketing authorization from the National Medical Products Administration on November 24, 2021, with a recommended dose of 40 mg QOD. Based on the safety data from 9 clinical studies that are conducted with HQP1351 and the safety and efficacy data of 36 patients already enrolled in this study, 40 mg QOD is selected as the dosage for adult subjects after discussion between the investigator and the sponsor. After the randomization of subjects at 30 mg, 40 mg and 50 mg QOD, with about 10 subjects in each group, it is planned to enroll 10-20 subjects in the non-randomized part to further explore the safety and efficacy of the drug, and the final number of enrolled subjects will be determined after discussion between the investigator and the sponsor according to the situation.

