#### **10.4 Statistical Analysis Method**

At the end of the study, safety and efficacy data will be analyzed. After comprehensive evaluation and comparison of efficacy, safety and PK data, 1 dose will be selected for Phase II studies.

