##### **10.4.3 Safety data**

All AEs will be coded according to Medical Dictionary for Regulatory Activities (MedDRA). The frequency (number and percentage of subjects) of subjects experiencing one or more AEs will be calculated and summarized by System Organ Class (SOC) and Preferred Term (PT). All AEs, drug-related AEs (AEs assessed as related or possibly related), AEs and SAEs graded based on NCI CTCAE, and AEs resulting in study withdrawal will be classified and summarized.

AEs and outliers (patient's physical examination results, vital signs, and laboratory results) determined by the investigator to be clinically significant will be summarized and tabulated by dose group.

Deaths, SAEs, and AEs leading to discontinuation of HQP1351 treatment will be listed in detail.

[figure not shown]

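### The 30 mg floor gives adults starting at 30, 40 and 50 mg none, one and two dose reductions, so AE-discontinuation rates and time on treatment are not comparable across the randomised arms

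*Protocol*

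**What the plan says.** - **Arms.** Section 5.4: "Each subject will be randomly assigned to a 30 mg, 40 mg, or 50 mg dose group". Section 10.1 plans "to randomize subjects into the 30 mg, 40 mg and 50 mg dose groups at the same time, about 10 subjects each".
- **Reduction rule.** Section 4.3.2: "Up to twice dose reductions are allowed, each to the next lower dose already explored".
- **Floor.** The same section continues: "Any adult subject requiring a reduction of HQP1351 dose below 30 mg QOD should permanently discontinue the study treatment".
- **Explored doses.** Section 1.5 reports 3, 11, 11 and 11 subjects at 20, 30, 40 and 50 mg by January 2021, so 20 mg had been explored.
- **Intolerable toxicity.** One of three alternative criteria in section 4.2 is "Toxicity requiring more than twice dose reductions of HQP1351". It is worded alike for every starting dose. Lines in Tables 2, 3 and 4 likewise refer to two reductions without mentioning the floor.
- **Low-dose option.** After an interruption of more than 14 days, section 4.3.1 allows an exception: "The subject can stay in the study to receive low-dose HQP1351 treatment". It gives no dose and does not say whether the floor applies.
- **Reporting.** Section 10.4.3 summarises AEs resulting in study withdrawal among other AE classes, and adds: "Deaths, SAEs, and AEs leading to discontinuation of HQP1351 treatment will be listed in detail".
- **Use.** Section 10.4: "After comprehensive evaluation and comparison of efficacy, safety and PK data, 1 dose will be selected for Phase II studies".

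**The concern.** Stopping treatment because of an AE is a natural measure of tolerability, and safety and tolerability by dose group is the primary objective (section 2.1). Here, whether a toxicity becomes a discontinuation depends on how many steps remain above the floor as well as on the drug. An event that Tables 2-4 manage by a lower dose is recorded as a dose reduction in a 40 or 50 mg subject and as an AE discontinuation in a 30 mg subject. Time on treatment carries the same artefact. With about 10 subjects per arm, two or three stops caused by the rule could change how the lowest dose looks when the doses are compared.

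The text is also hard to apply. For an adult at 30 mg, the next lower explored dose is 20 mg under one rule and is barred by the next. The low-dose option may or may not cross the floor.

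**Working it through.** **The plan's own figure.** Section 1.5.2 gives 5 AE discontinuations (14%) among 36 GIST subjects. Check: 3 + 11 + 11 + 11 = 36, and 5/36 = 13.9%. It reproduces, but that analysis combines the four dose groups, so it gives no rate by dose.

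**Permitted reductions.** Step down the explored levels 20, 30, 40 and 50 mg with a cap of two.

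| Start | With the 30 mg floor | Without the floor |
|---|---|---|
| 30 mg | 0 | 1 |
| 40 mg | 1 (to 30) | 2 (to 30, 20) |
| 50 mg | 2 (to 40, 30) | 2 (to 40, 30) |

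**Effect on AE discontinuation.** Let q be the chance, at a given dose, of a toxicity managed by reduction, and s the chance of one that stops treatment at any dose. Both are assumptions; the protocol gives neither. With successive events independent:

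- A30 = s30 + q30
- A40 = s40 + q40 × A30
- A50 = s50 + q50 × A40

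The first-event count (reduction or discontinuation, at the assigned dose) is s + q in each arm.

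| Assumed q at 30/40/50 | Assumed s at 30/40/50 | AE discontinuation | First-event count |
|---|---|---|---|
| 30/30/30% | 0 | 30/9/2.7% | 30/30/30% |
| 20/30/40% | 0 | 20/6/2.4% | 20/30/40% |
| 20/30/40% | 5/5/5% | 25/12.5/10% | 25/35/45% |
| 10/20/30% | 5/10/20% | 15/13/23.9% | 15/30/50% |

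Second row: 0.30 × 0.20 = 0.06 and 0.40 × 0.06 = 0.024. With 10 subjects per arm that is 2.0, 0.6 and 0.24 expected discontinuations. Fourth row: 0.10 + 0.20 × 0.15 = 0.13 and 0.20 + 0.30 × 0.13 = 0.239.

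**Reading the table.**

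- Rows two and three reverse a true upward gradient.
- In row four 50 mg remains worst, while 30 and 40 mg change places. The order of those two would be kept if s40 exceeded 0.15 × (1 − 0.20) = 12%.
- If each patient instead has a fixed tolerance threshold, only those who cannot tolerate 30 mg eventually stop. All arms then show q30, so a 20/30/40% gradient is flattened to 20/20/20%.
- For some toxicities the tables stop treatment on recurrence whatever steps remain (Grade 4 platelets, Grade 3 febrile neutropenia, Grade 3 bilirubin, Grade 3 AST/ALT). With the second-row q and s = 0, the rates are then 20%, 0.30 × 0.20 = 6% and 0.40 × 0.30 = 12%.

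In every case 30 mg shows its full first-event rate. The other two arms show no more than theirs, and usually less, because q is multiplied by a further probability that cannot exceed 1.

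**The case against.** **A cap is not a promise.** Two reductions is a maximum, and a maximum can coexist with a minimum dose. This stands: a reader might infer that every subject is guaranteed two reductions, or that 4.2 declares toxicity intolerable only after a third. The text says neither, and 4.2 has two other criteria, one of them discretionary. What remains is that the floor overrides the next-lower-explored-dose wording at 30 mg, and that the two-reduction lines do not acknowledge it.

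**Not every toxicity is affected.** This stands. Grade 4 febrile neutropenia, anaemia, bilirubin, AST/ALT and other toxicities stop treatment in every arm. A first Grade 3 platelet or neutrophil event restarts at the original dose in every arm.

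**Discontinuation is one input among several.** This stands. A reader might infer that the whole tolerability comparison behind the RP2D is biased. The documents do not support that. The floor does not alter the definitions of AE incidence, grade, SAE or laboratory summaries. Section 4.4 makes the RP2D a joint judgement on safety, tolerability, PK and efficacy, with no discontinuation-rate rule. Longer exposure after a reduction can also add AEs to the 40 and 50 mg arms, which works the other way.

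**PFS is not cut short by early stopping.** This also stands. Sections 7.7.2.1 and 8 continue tumour assessment every 8 weeks after discontinuation, until progression or new therapy.

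**Randomisation is over, and table layout belongs to the SAP.** Section 1.5.2 says no further randomisation will take place and that 40 mg has been chosen for later adults. Rewording cannot change completed treatment, but section 10.4 still places the dose comparison at the end of the study. A full table specification can wait for the SAP. The imbalance itself comes from the protocol's own rules.

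**Discretion may soften the floor.** The exceptions in 4.2 and 4.3.1 could keep some subjects on drug. How often they would apply cannot be known from the document.

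**Conclusion.** The point holds as a moderate one. The 0, 1 and 2 count follows directly from 4.3.2 and needs no assumption. AE discontinuation and time on treatment are therefore not comparable across the randomised arms, and they are distorted against 30 mg relative to the true gradient.

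The size is unknown. The illustrations rest on assumed toxicity rates and, except for the fixed-threshold case, on independent successive events. Depending on those inputs the ranking may be reversed, flattened or unchanged. A reader might infer that 30 mg must look least tolerable, or has already been disadvantaged. Neither follows: reversal is only one outcome, the observed 5 of 36 is not split by dose, and section 1.5.2 describes 30, 40 and 50 mg alike as well tolerated.

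**What to change.** 1. In 10.4.3, add by assigned starting dose the proportion of subjects with a first drug-related AE calling for dose reduction or permanent discontinuation. Use it instead of AE discontinuation alone when tolerability is compared across doses for the RP2D.
2. Show AE discontinuation beside the number of reductions permitted in each arm (0, 1, 2), and do not read it or time on treatment as a direct dose comparison.
3. Reconcile the floor in 4.3.2 with the next-lower-explored-dose wording in that section, the two-reduction wording in 4.2 and Tables 2-4, and the low-dose option in 4.3.1, so that each starting dose has one stated number of steps. Which clinical rule applies is for the sponsor and investigators; no view is taken here.

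The cost is some wording in 4.2-4.3 and one added safety summary. It uses AE severity, relatedness and dose changes, which section 13.2 already requires to be recorded. The downside is that the combined count will be higher, and look less favourable, than AE discontinuation alone.

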| Grade 2 ( $\geq 1.0$ - $< 1.5 \times 10^9/L$ )                                                                                                                    | No dose adjustment required.                                                                                                                                                                                                                                                                                                                                                                                                                                                                                                                                                                                                              |
| Grade 3 ( $\geq 0.5$ - $< 1.0 \times 10^9/L$ )                                                                                                                    | 
 
1. Interrupt HQP1351 administration until toxicity resolves to <math>\geq 1.0 \times 10^9/L</math>.
 
2. Restart HQP1351 administration at the original dose level.
 
3. If Grade 3 toxicity recurs, interrupt HQP1351 administration until toxicity resolves to <math>\geq 1.0 \times 10^9/L</math>. 
 
a) If the duration is less than or equal to 7 days, resume administration at the original dose level.
 
b) If the duration is greater than 7 days, resume HQP1351 administration at a reduced dose level.
 
 
 
 |
| Grade 4 ( $< 0.5 \times 10^9/L$ )                                                                                                                                 | 
 
1. Interrupt HQP1351 administration until toxicity resolves to <math>\geq 1.0 \times 10^9/L</math>.
 
2. Restart HQP1351 administration at a reduced dose level.
 
3. If Grade 4 toxicity recurs, interrupt HQP1351 administration until toxicity resolves to <math>\geq 1.0 \times 10^9/L</math>, and resume administration at a reduced dose level.
 
4. A maximum of two dose reductions is allowed.
 
                                                                                                                                                            |

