| Febrile neutropenia                                                                                                                                        |                                                                                                                                                                                                                                                                                                                                                                                                                                                                                                                                                                                                                                           |
| Grade 3: ANC $< 1.0 \times 10^9/L$ accompanied by single body temperature $> 38.3^\circ\text{C}$ or body temperature $\geq 38^\circ\text{C}$ for more than 1 hour | 
 
1. Interrupt HQP1351 administration until ANC recovers to <math>\geq 1.0 \times 10^9/L</math> and there is no fever.
 
2. Restart HQP1351 administration at a reduced dose level.
 
3. If febrile neutropenia recurs, stop HQP1351 administration.
 
                                                                                                                                                                                                                                                                                                                        |
| Grade 4: life-threatening, urgent intervention indicated                                                                                                          | Stop HQP1351 administration.                                                                                                                                                                                                                                                                                                                                                                                                                                                                                                                                                                                                              |

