| Anemia (Hemoglobin)                                                                                                                                        |                                                                                                                                                                                                                                                                                                                                                                                                                                                                                                                                                                                                                                           |

[figure not shown]

| Toxicity / NCI-CTCAE grade                               | Actions to be taken                                                                                                                                                                                                |
|----------------------------------------------------------|--------------------------------------------------------------------------------------------------------------------------------------------------------------------------------------------------------------------|
| Grade 1 ( $\geq 10.0$ - LLN g/dL)                        | No dose adjustment is required.                                                                                                                                                                                    |
| Grade 2 ( $\geq 8.0$ - $<10.0$ g/dL)                     | No dose adjustment is required.                                                                                                                                                                                    |
| Grade 3 ( $<8.0$ g/dL)                                   | 
 
1. Interrupt HQP1351 administration until toxicity resolves to Grade <math>\leq 2</math>.
 
2. Restart HQP1351 administration at the original dose level.
 
 |
| Grade 4: life-threatening, urgent intervention indicated | Stop HQP1351 administration.                                                                                                                                                                                       |

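### Sections 4.3.1 and 4.3.2 and Table 2 set different restart levels after Grade 3/4 neutropenia and Grade 3 anemia, and no sentence says which prevails

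*Protocol*

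**What the plan says.** **General rule.** The third paragraph of 4.3.2 deals with drug-related Grade 3 or 4 toxicity. Drug is stopped at once, may stay off for at most 14 days, and then: "The investigational drug can be resumed when the toxicities resolve to Grade 1 or below, or baseline level". Section 4.3.1 gives the same recovery target and limit, and adds: "If HQP1351 is discontinued for more than 2 weeks (14 days), the subject will be withdrawn from the study". The one exception needs the agreement of the principal investigator and the sponsor: "The subject can stay in the study to receive low-dose HQP1351 treatment". The first paragraph of 4.3.2 states the general rule without a baseline alternative: "The study drug can be resumed when the study drug-related toxicities resolve to grade 1 or below".

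**Table 2.** For Grade 3 and Grade 4 neutropenia the instruction is "Interrupt HQP1351 administration until toxicity resolves to \geq 1.0 \times 10^9/L". For Grade 3 febrile neutropenia it begins "Interrupt HQP1351 administration until ANC recovers to", gives the same ANC and adds that fever must be gone. For Grade 3 anemia it is "Interrupt HQP1351 administration until toxicity resolves to Grade \leq 2".

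**Link between the two.** The only one is the last sentence of the 4.3.2 text: "Please refer to Table 2-4 for guidance on dose adjustment for study drug-related toxicity". It makes no exception to the general rule and sets no order of precedence.

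**Separate item.** Section 9.5(3), under anemia, prohibits colony stimulating factor in Cycle 1. Section 9.5(4), under neutropenia, says that neutrophil colony stimulating factors are used in Cycle 1.

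**The concern.** By Table 2's own grade bounds, ANC 1.0 to <1.5 × 10^9/L and Hb 8.0 to <10.0 g/dL are Grade 2. The table therefore restarts drug at a grade that the text does not accept as recovery. Two sites with the same blood count can act differently and both be within the protocol: one restarts, the other keeps holding and, after 14 days, withdraws the subject unless a low dose is agreed. That exception leaves little room for an adult on 30 mg QOD, because 4.3.2 ends treatment for an adult who needs less than 30 mg.

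Safety and tolerability are the primary endpoint (10.2.1), the recommended Phase II dose rests partly on them (4.4), and 10.4.3 plans a summary of AEs resulting in study withdrawal. Withdrawals that depend on which rule a site follows would add noise to that summary.

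The clash in 9.5 also touches ANC recovery. A site that follows 9.5(4) as printed could mask neutropenia in the first cycle.

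**Working it through.** No figure of the plan has to be reproduced. The check sets the restart levels side by side and asks whether the baseline alternative removes the difference.

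**Step 1. Restart levels.**

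| Toxicity | Text (4.3.1; 4.3.2, third paragraph) | Table 2 |
|---|---|---|
| Platelets, Grade 3/4 | Grade 1 or less, or baseline | Grade 1 or less |
| Neutropenia, Grade 3/4 | Grade 1 (ANC ≥1.5), or baseline | ANC ≥1.0 |
| Febrile neutropenia, Grade 3 | Grade 1 (ANC ≥1.5), or baseline | ANC ≥1.0 and no fever |
| Anemia, Grade 3 | Grade 1 (Hb ≥10.0 g/dL), or baseline | Hb ≥8.0 g/dL |

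Platelets raise no comparable gap. The other three rows differ.

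**Step 2. Does the baseline alternative close the gap?** Inclusion criterion 5 (3.1) requires ANC ≥1.5 × 10^9/L and hemoglobin ≥90 g/L, which is 90/10 = 9.0 g/dL. I assume that the baseline value meets the entry floor. Write B for baseline.

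- ANC: text level = min(1.5, B), with B ≥1.5, so 1.5. Table level = 1.0. The rules disagree for ANC 1.0 to <1.5, a width of 1.5 − 1.0 = 0.5. Baseline never narrows this.
- Hb: text level = min(10.0, B), with B ≥9.0. Table level = 8.0. The rules disagree from 8.0 up to min(10.0, B).
  - B ≥10.0: 8.0 to <10.0, width 10.0 − 8.0 = 2.0.
  - B = 9.0: 8.0 to <9.0, width 9.0 − 8.0 = 1.0.

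For anemia the gap narrows at low baselines but never vanishes.

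**Step 3. The same count under each rule.** ANC recovers to 1.2 after a first Grade 3 neutropenia: Table 2 restarts at the original dose, while the text's restart level is not met. Hb recovers to 8.5 g/dL after Grade 3 anemia: Table 2 restarts at the original dose, while the text's level is not met for any eligible baseline. For Grade 4 neutropenia and febrile neutropenia the Table 2 restart is at a reduced dose, with the same disagreement about when.

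**Step 4. The 14-day limit.** The neutropenia, febrile neutropenia and anemia rows carry no limit on the length of the hold. The only limit is the 14 days in the text, and the text ties it to the Grade 1/baseline target. Even a reader who takes the restart level from Table 2 is not told which target the 14 days refer to.

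**Step 5. How often?** Section 1.5.2 allows only ceilings, from the first 36 GIST subjects.

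- Anemia of any grade and cause: 41.7%, that is 15/36. The conflict needs drug-related Grade 3 anemia, for which no rate is given.
- Decreased neutrophils are not among the events listed at ≥20%. Since 7/36 = 19.4% and 8/36 = 22.2%, at most 7/36 had them, if that list is complete and correct as printed.

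The floor is zero for both.

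**The case against.** The strongest reply is that the ordinary reading already settles the matter. Section 4.3.2 states a general rule and then sends the reader to tables with toxicity-specific actions. Their restart levels vary by toxicity, which looks like deliberate tailoring. Table 2 is also coherent in itself: Grade 2 neutropenia and Grade 2 anemia need no dose adjustment, so restarting there is consistent. The text is moreover permissive: it says when drug can be resumed and does not add that it can be resumed only then. Most of this stands, and it makes Table 2 the probable intent. It does not supply the missing sentence. The text calls the tables guidance, states its own rule without exception, and attaches the 14-day limit to its own target.

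Four stronger readings are tempting and are not supported:

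- *Three restart levels for a subject who enters with Hb 9.0 to <10.0.* The first paragraph of 4.3.2 is general. The third is specific to Grade 3/4 events and adds the baseline alternative, so it displaces the first. Two levels remain, and the first paragraph needs only a wording alignment.
- *Half a cycle's doses lost.* A 28-day QOD cycle has 14 doses and any 14 consecutive days hold 7 of them, so a full hold costs 7/14 = 50%. That is the cost of one full hold under the text. It is not the difference between the rules, because the time to reach ANC 1.0 or Hb 8.0 is unknown.
- *A material distortion of the primary endpoint.* The Grade 3/4 event is recorded and summarized by grade under either rule, and 10.4.3 names no summary of interruptions. Only the withdrawal summary and the listing of discontinuations could change. For that, the count must stay in the disputed range through day 14, the site must set the table row aside, and the low-dose exception must not be used.
- *15/36 or 7/36 as an estimate of subjects affected.* Both are ceilings on broader events.

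**Conclusion.** The dosing instructions are wrong as written, to a minor to moderate degree. For drug-related Grade 3/4 neutropenia, Grade 3 febrile neutropenia and Grade 3 anemia, the text and Table 2 give different restart levels and neither is said to prevail. The disagreement covers ANC 1.0 to <1.5 × 10^9/L, and Hb from 8.0 g/dL up to the lower of 10.0 g/dL and baseline, a range 1.0 to 2.0 g/dL wide. This rests on the grade bounds in Table 2 and on baseline values that meet the entry criteria. How many subjects are affected cannot be derived from the protocol and may be none, and the effect is nil if all sites follow Table 2. The point is worth making because these are operative safety instructions and the correction is nearly free.

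The clash between 9.5(3) and 9.5(4) is a separate error. It stands on its own and adds no weight to the restart point.

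**What to change.** 1. In 4.3.1 and 4.3.2, state that a restart threshold given in Tables 2-4 overrides the general Grade 1/baseline rule, and that it is also the recovery target for the 14-day limit.
2. In 4.3.2, use one wording for toxicities without a table threshold, namely Grade 1 or below, or baseline, in both the first and the third paragraph.
3. Separately, correct 9.5(4) to say that neutrophil colony stimulating factors are prohibited in Cycle 1, in agreement with 9.5(3).

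The cost is a precedence sentence in each of two sections, one wording alignment and one correction. No visits, tests or subjects are added.
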